### Follow-up

Outcomes will be counted in a follow-up window to 24 months postindex prescription, death, exit from BC or the end of the study window. We will censor follow-up for death or departure from the province, but not clinical outcomes, in order to gather information on the clustering of important clinical events (eg, patient has a bleed, discontinues warfarin, then has a vascular event and dies).

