### Analysis plan

The primary analysis will be intention-to-treat, meaning that if the index prescription is for warfarin, then any outcome events are attributed to warfarin whether switching occurs or not. This mimics the conservative, recommended analysis in clinical trials. However, this approach may underestimate benefit and harm, therefore a secondary ‘as-treated’ analysis will explore outcomes based on actual treatment during follow-up. Although both analyses occur after baseline confounders are adjusted for, the as-treated analysis requires further adjustments for measured time-varying confounding and selection bias using inverse-probability weighting.^34^ Switching between anticoagulants will be further explored by examining comparative duration on each anticoagulant as well as switch frequency.

For the main analysis, the effects of treatment with the use of DOACs versus warfarin will be estimated from time-to-event models (Cox proportional hazards or Poisson). Risk modifying effects such as age, sex, dose and risk factors (including congestive heart failure, hypertension, diabetes, prior stroke, prior major bleed, renal or liver failure, interacting concomitant medications, alcohol abuse) will be evaluated using tests of interaction. Tests of interaction will be used to identify key subgroups in which warfarin may be better than DOACs or DOACs better than warfarin, using the two coprimary outcomes and net clinical benefit as defined above. Models can simultaneously control for potential confounders such as cardiovascular disease, rural/remote location of residence, physician practice—all estimated at index date (further details in online supplementary appendix 1). Sample size is unlikely to allow individual DOAC versus DOAC comparison, but outcomes will be tabulated by individual drug.

Community-based outcome event rates and the RE-LY trial suggest a coprimary outcome event rate of ∼12% per year for warfarin versus 10% per year for DOACs.^3^
^35^ Assuming conservatively that accrual extends over 3 years and that patients have a minimum of 1 year of follow-up, and that 67% of the sample is on warfarin, an analysis based on outcomes at 1 year would require 6000 patients on warfarin and 3000 patients on DOACs for 80% power. Since our analysis will be time-to-event rather than using binary outcomes at 1 year, we expect to have greater power than estimated.

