### Control for confounding

New users of DOACs are likely to differ in several characteristics from new users of warfarin. We expect them to be younger and with less comorbidity. To control for confounding, we will adjust estimates by age, sex and propensity score. Propensity scores will be computed by multiple logistic regression of the logit of the conditional probability of allocation to warfarin versus any DOAC (conditional on patient being a new user of either anticoagulant) regressed on potential confounders at baseline. Among the variables considered will be sex, dose, CHADS_2_ (Congestive heart failure, hypertension, age, diabetes, stroke - 2 points) score, and HAS-BLED score (hypertension, abnormal renal or hepatic function, previous stroke, bleeding, labile INR, age, drugs/alcohol), other vascular events, concomitant medications, drug plan coverage, remote location, neighbourhood income quintile, physician specialty, haemoglobin and year of cohort entry. We plan to evaluate conventional and high-dimensional propensity scores, the latter estimated using preselected and empirically chosen variables from medication, hospital and medical services data.^37^

Analyses of switching patterns, including the duration of OAC exposure and the switching frequency, will be treated as time-dependent confounders and controlled by marginal structural modelling.^38^

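### The marginal structural model sentence assigns treatment history (duration and switching) the role of time-dependent confounder, which does not fit the weighting promised for the secondary as-treated analysis

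*Protocol article*

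**What the plan says.** The Analysis plan section makes intention-to-treat by index prescription the primary analysis ("The primary analysis will be intention-to-treat"). It says this may understate benefit and harm, so "a secondary ‘as-treated’ analysis will explore outcomes based on actual treatment during follow-up". On adjustment, it says that "both analyses occur after baseline confounders are adjusted for" and that "the as-treated analysis requires further adjustments for measured time-varying confounding and selection bias using inverse-probability weighting". It gives switching a descriptive role as well: "Switching between anticoagulants will be further explored by examining comparative duration on each anticoagulant as well as switch frequency".

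The Control for confounding section describes a propensity score for warfarin versus any DOAC, "regressed on potential confounders at baseline". It closes by saying that analyses of switching patterns, including "the duration of OAC exposure and the switching frequency, will be treated as time-dependent confounders and controlled by marginal structural modelling".

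The Follow-up section explains that follow-up continues after clinical events so that sequences of events can be seen. Its example is "patient has a bleed, discontinues warfarin, then has a vascular event and dies".

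**The concern.** A marginal structural model estimates the effect of a treatment history. Its weights remove the influence of factors that arise during follow-up, drive the next treatment decision and also predict outcome. When exposure is defined by actual treatment, switching, stopping and time on each drug make up that exposure. The closing sentence of Control for confounding puts them in the confounder's place.

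This is a role stated wrongly, which is different from a list left for another document. That sentence is the only place in the article that says what the time-dependent confounders are. The clinical covariates named elsewhere are fixed at baseline or at the index date. An analyst who reads the weighting commitment in the Analysis plan and then looks up which variables it concerns is sent to the wrong ones.

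At stake is the analysis offered as the counterweight to intention-to-treat dilution, for bleeding as well as for stroke and embolism. If the reasons for switching stay uncontrolled, the as-treated comparison can be biased, with a direction that depends on who switches.

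**Working it through.** **Reading the sections together**

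| Element | Role in an as-treated marginal structural model | Role in the article |
|---|---|---|
| Drug taken over time, stopping, switching, duration | Treatment history | Exposure (Analysis plan); time-dependent confounder (Control for confounding) |
| Post-index event that prompts stopping and predicts outcome, such as a bleed | Time-dependent confounder | Appears in the Follow-up example; not named for the model |
| Baseline covariates | Baseline confounders | Propensity score, used for both analyses |

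In the Follow-up example the bleed is the confounder and the discontinuation is the treatment change. The closing sentence of Control for confounding names the second kind of variable and not the first.

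**Why history-only weights cannot help**

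Let A0 be the starting drug, A1 later treatment and L a clinical factor arising between them. Stabilised weights are

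SW = P(A1 | A0) / P(A1 | A0, L).

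If L is left out of the denominator, SW = P(A1 | A0) / P(A1 | A0) = 1 for everyone. Without stabilisation, the weight is still a function of (A0, A1) only. It is then constant among patients who share a treatment history, so it cannot change how common L is in that group. The risk within each history stays as it was.

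**Illustration (all parameters assumed; none comes from the article)**

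- A0 = 1 (DOAC) in 33%, A0 = 0 (warfarin) in 67%.
- P(L = 1) = 0.15 if A0 = 1, and 0.20 if A0 = 0.
- P(A1 = 1): 0.95 without L and 0.70 with L if A0 = 1; 0.05 and 0.30 if A0 = 0.
- Outcome risk: 0.05 without L and 0.20 with L. Later treatment has no effect, so the true difference for A1 is 0.

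DOAC starters:
- P(A1 = 1) = 0.85 × 0.95 + 0.15 × 0.70 = 0.9125.
- P(L | A1 = 1) = 0.105 / 0.9125 = 0.115; P(L | A1 = 0) = 0.045 / 0.0875 = 0.514.
- Risks: 0.05 + 0.15 × 0.115 = 0.067 and 0.05 + 0.15 × 0.514 = 0.127. Difference -0.060.

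Warfarin starters:
- P(A1 = 1) = 0.80 × 0.05 + 0.20 × 0.30 = 0.10.
- P(L | A1 = 1) = 0.06 / 0.10 = 0.600; P(L | A1 = 0) = 0.14 / 0.90 = 0.156.
- Risks: 0.140 and 0.073. Difference +0.067.

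A linear model in A0 and A1 pools these with weights P(A0) × p × (1 - p), where p is P(A1 = 1):
- 0.33 × 0.9125 × 0.0875 = 0.0263 and 0.67 × 0.10 × 0.90 = 0.0603.
- Pooled = (0.0263 × -0.0599 + 0.0603 × 0.0667) / 0.0866 = +0.028.

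A simulation of 2,000,000 patients agrees within sampling error:

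| Weights | Estimated difference for A1 | Exact value |
|---|---|---|
| None | +0.027 | +0.028 |
| Treatment history only, stabilised | +0.027 | +0.028 |
| Treatment history plus L | -0.001 | 0 |

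The differences have opposite signs in DOAC and warfarin starters, so the direction of the net bias depends on the pattern of switching.

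A second simulation used 300,000 patients, 8 quarters, a null effect and a clinical factor with outcome risk ratio 3 that prompts DOAC-to-warfarin switching. The as-treated odds ratio was 0.92 unweighted, 0.92 with weights from duration and switch count only, and 1.00 with the factor in the denominator.

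**The plan's own figure**

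The article gives 6000 warfarin and 3000 DOAC patients for 80% power at 12% versus 10%. The usual two-proportion formula gives 5822 and 2911, and power of 81.2% at 6000 and 3000. The figure reproduces and does not bear on this point.

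**The case against.** A reader might infer that the as-treated analysis is left unadjusted. The article does not support that. The Analysis plan keeps baseline adjustment for both analyses and commits to weighting for measured time-varying confounding and selection bias. Weighting done as that section says would control the confounding, provided the relevant factors are measured and included. The closing sentence of Control for confounding is also loosely built: it does not say that the weights use only duration and switch count, and it may refer to the separate exploration of switching. These objections stand, and they limit the finding to a mismatch between two sections and to what follows if the second is taken literally.

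A missing list of weight-model covariates is no fault by itself. It may sit in the appendix or an analysis plan that is not shown. What remains is that the article names variables for the role, and they are the wrong ones.

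Past duration and past switches can predict both current treatment and outcome, so they belong in the weight model. That is right, but they belong there as treatment history alongside the clinical predictors, not in their place. Nor does conditioning on past history always remove the effect of current treatment, so a general claim that it adjusts the effect away would go too far.

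Finally, a reader might take 0.92 or +0.027 as the bias to expect here, or take weights of exactly 1 as a certain outcome. The parameters are assumed, and the article specifies neither stabilisation nor a numerator. Only the failure of history-only weights to remove the confounding is general.

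**Conclusion.** The point holds in a limited form. The article gives treatment history the role of time-dependent confounder, and this does not fit its own commitment to weight for measured time-varying confounding. Followed literally, with weights from treatment history alone, the as-treated estimate would keep the confounding by reasons for switching or stopping. The size of that bias cannot be derived from the article.

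The conclusion rests on two readings: that the marginal structural model serves the as-treated or switching analyses, and that the sentence is taken to define the confounders. The effect is confined to those secondary analyses. The intention-to-treat comparison of both coprimary outcomes, the propensity score and the sample size are untouched. The sentence should be corrected, at a severity below must-fix.

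**What to change.** Replace the closing sentence of Control for confounding with wording to this effect:

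- Switching, stopping and duration on each anticoagulant form the time-varying treatment process, or the artificial-censoring process if follow-up is censored at a change of treatment.
- The inverse-probability weights use measured post-index clinical predictors of both treatment change and outcome, such as an interim bleed, taken from the linked hospital, dispensing, billing and laboratory data.
- Past treatment history enters both the numerator and the denominator of stabilised weights.
- Duration and switch frequency are reported descriptively, as the Analysis plan already intends.

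The full covariate list can stay in the appendix or analysis plan. The cost is one sentence of wording. The data sources are those already listed under Study cohort, and the primary analysis does not change.

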## Ethics and dissemination

Required ethics approvals from Hamilton Integrated Research Ethics Board Application #16-643-C and UBC Clinical Research Ethics Board Application #H13-00868, and data sharing agreements with PopData-BC and LifeLabs Medical Laboratory Services, have been obtained prior to this study. Secure access and storage of data and data linkage are governed by Population Data BC. The necessary data access request templates, privacy impact analyses and research service agreements are complete.

Results will be published in a peer-reviewed journal electronically and in print. They will also be disseminated to the national drug plan managers and to the national drug safety and effectiveness leaders. The study results will be an important addition to the literature and for policymakers for four main reasons: (1) the usage of the DOACs has increased sharply since their launch adding more than US$100 million annually to public plan drug budgets in Canada, (2) their comparative efficacy and safety in pivotal trials was near identical for countries with high-quality warfarin management thus bringing cost-effectiveness into question, (3) the OACs overall are a very high benefit/high harm class of drugs and (4) our study using universal population coverage data will avoid biases present in other real-world studies.
